### Evaluation of coronary artery disease

At the first (screening) visit, all selected subjects will be evaluated for CAD using the treadmill stress test. Subjects with abnormal stress test results, including typical chest pain, with ST segment depression ≥1 mm, or with a horizontal or descending trace on the electrocardiogram for a duration of 0.08 s after the J point, will be excluded. When necessary, individuals will be submitted to other tests to evaluate CAD, such as myocardial scintigraphy and coronary angiography.

### Measurement of blood pressure including 24-h ambulatory blood pressure monitoring

After randomization and again after 12 weeks of treatment with vildagliptin (Group 1) or glibenclamide (Group 2), 24-h non-invasive ambulatory blood pressure monitoring (ABPM) will be performed on a workday with a portable compact digital BP recorder (Mobil-O-Graph^®^ 24-hour PWA monitor).

Automatic BP measurements will be recorded at 20-min intervals for diurnal readings (7.00 a.m.–11.00 p.m.) and at 30-min intervals for nocturnal readings (11.00 p.m.–7.00 a.m.). Nighttime and daytime periods will be assessed based on information reported by the subjects. The sleep BP will be defined as the mean BP from the time the subjects go to bed until the time they get up. The daytime BP will be defined as the average BP during the rest of the day. The subjects will be divided into two groups according to the dip in SBP during the nighttime: participants will be considered as dippers, if the decrease in sleep SBP is ≥10 % and non-dippers if the decrease is <10 %. As part of the exam protocol, all participants will be requested to make a note of their daily activities, their meal times, times of sleeping and waking up, as well as time of taking medications and the presence of symptoms.

### Vascular tests

Vascular tests will be performed in the subjects of both groups at the first visit and after 12 weeks of treatment.Determination of endothelial function

Peripheral arterial tonometry (Endo-PAT 2000; Itamar Medical, Caesarea, Israel) is a non-invasive peripheral test of endothelial function [32]. The PAT device is placed on the tip of each index finger and comprises a pneumatic plethysmograph that applies a uniform pressure to the surface of the distal finger, allowing measurement of pulse volume changes. The inflation pressure of this digital device is electronically set at 10 mmHg below DBP or 70 mmHg. The PAT signal is recorded at baseline and then after 5 min of arterial occlusion using an inflatable cuff, while the contralateral arm serves as a control. The blood pressure cuff is inflated to 60 mmHg higher than systolic pressure or at least 200 mmHg. Lack of residual pulsatility is monitored throughout the occlusion period. Post-occlusive hyperemia stimulates endothelium-dependent vasodilatation, causing an increase in digital pulse amplitude. Pulse amplitude is recorded electronically in both fingers and analyzed by an automated, computerized algorithm (Itamar Medical). The change from the baseline measurement is expressed as the RHI, which, in part, reflects vasodilator function of the digital microcirculation.

Subjects will be instructed to fast the night before testing and to refrain from ingesting alcohol or caffeine. The room temperature will be maintained between 21 and 24 °C at all times during the exam; restrictive clothing, watches, rings, or other jewelry on the hands that might interfere with blood flow will be removed. The test will be performed in the morning after the patient has been comfortably seated or has laid down in the study room for at least 15 min to reach a relaxed cardiovascular steady-state [31, 32]. The subjects of the study will be submitted to the endothelial function test at their first visit and after 12 weeks of treatment. Endothelial dysfunction will be defined as a RHI ≤ 1.68, according to a study performed in healthy asymptomatic control individuals without history of CVD and without major risk factors [56].2.Determination of the central aortic pressure and vascular stiffness

Arterial stiffness, assessed using the non-invasive method of radial artery applanation tonometry, is predictive of vascular disease. A portion of the artery pressure wave travelling towards the extremities is reflected back by peripheral impedance points. In healthy individuals, the reflected wave returns to the aorta during diastole. However, when arteries become stiff, the transit time between the incident and reflected waves is reduced. Thus, the reflected wave returns to the aorta during systole of the same cardiac cycle thereby augmenting the central BP. This elevation of the central BP can be quantified using the AIx [57, 58]. The AIx is associated with cardiovascular risk, and predicts the presence or absence of CAD [59]. Higher values of the AIx indicate increased wave reflection from peripheral vessels or earlier return of the reflected wave as a result of increased pulse wave velocity, which is attributed to an increased arterial stiffness. In young healthy individuals, the systolic arterial pressure (aortic) is about 15–20 mmHg lower than the peripheral systolic pressure (brachial) [45, 60].

## Outcomes and outcome adjudication

Change in the RHI from baseline after 12 weeks of vildagliptin vs. glibenclamide treatment.Change in the central blood pressure from baseline to after 12 weeks of vildagliptin vs. glibenclamide treatment.

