## Randomization and follow-up

After screening for eligibility, 50 individuals will be submitted to an evaluation of endothelial function using the Endo-PAT 2000 device and measurement of the arterial stiffness by applanation tonometry of radial artery. Subsequently, they will be randomly allocated to the two arms of the study: Group 1 will receive vildagliptin (100 mg/day b.i.d.) added-on to metformin (500–2550 mg/day according to glycemic control) and Group 2 will receive glibenclamide (5–20 mg/day according to glycemic control) added-on to metformin (500–2550 mg/day according to glycemic control). Blood samples will be collected after 12-h overnight fasting at screening visit and then after 12 weeks of treatment with vildagliptin (Group 1) or glibenclamide (Group 2). Renin-angiotensin system blockers will be prescribed to all subjects at the screening visit and all other antihypertensive drugs will be maintained. Subjects will have three return consultations. The first will be to randomize patients to Group 1 or 2 and they will be evaluated after four and 12 weeks. Compliance will be monitored by pill counts at the second and last visits. The glycemic control will be evaluated by glycated hemoglobin and fasting glucose. Adverse events will be evaluated on the basis of spontaneous reports and interviews by the investigator. Considering side effects and safety, nausea, upper abdominal pain and flatulence are expected, although uncommon, while taking vildagliptin. The most frequent side effect of glibenclamide is hypoglycemic events. Changes in blood count, renal function, and liver function are not expected with either treatment.

Table 2 shows a summary of key practical aspects of the study with all follow-up visits and requested exams.

**Table 2 Tab2:** Key practical aspects of the study with all the clinical visits and the requested exams

Visits	Screening	Visit 1	Visit 2	Visit 3
Weeks	−1	1	4	12
Informed consent	X			
Inclusion and exclusion criteria	X	X		
Medical history	X			
Medical evaluation/physical examination	X	X	X	X
Randomization		X		
Pregnancy test	X			
Creatinine	X			X
Fasting glucose	X		X	X
Ultrasensitive C-reactive protein	X			X
Total cholesterol	X			X
High-density lipoprotein cholesterol	X			X
Triglycerides	X			X
Glycated hemoglobin	X			X
Alanine aminotransferase	X			X
Microalbuminuria	X			X
Ambulatory blood pressure monitoring		X		X
Treadmill test	X			
Determination of the central aortic pressure and vascular stiffness markers		X		X

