## Statistical considerations

### Sample size and power calculations

The site http://www.lee.dante.br-pesquisa was used to estimate the sample size, considering a 30 % change in the RHI between treatment groups as clinically relevant. Assuming a standard deviation of 0.3 would require a total of 21 subjects to detect a 30 % change in the RHI with a power of 80 % at a significant level of 0.05. However, considering a potential 20 % of drop-out or lost to follow-up rate, a total of 50 patients (25 for each group) will be considered.

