### Statistics

All analysis will be performed using SPSS Statistical Software (IBM SPSS Statistics for Windows, Version 21.0. Armonk, NY: IBM Corp.). Continuous variables will be presented as mean ± SD and categorical variables as frequencies. Differences between the both groups at baseline will be evaluated by unpaired *t* test or the Mann–Whitney test for comparison of continuous variables. The Chi square test or Fisher’s exact test will be employed to compare categorical variables. The change from baseline to 12-weeks follow-up in the both groups will be evaluated using the paired *t* test for continuous variables. Pearson’s correlation will be used to assess the relationship between HbA1c and RHI and AIx, after confirmation of similarity between groups in respect to demographic data (age, gender, GFR, and comorbidities: hypertension and dyslipidemia) and HbA1c targets after 12 weeks of considered treatment. Thus, the Pearson’s correlation obtained will be potentially consequent to distinct therapeutic responses. For all analysis, a 2-sided *P* < 0.05 will be considered statistically significant.

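### The tests named for change in RHI and central pressure use no baseline covariate; adjusting for the baseline already collected would be more precise, by an amount the protocol's figures do not settle

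*Protocol article*

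**What the plan says.** Under Outcomes and outcome adjudication, the protocol article lists two outcomes: "Change in the RHI from baseline after 12 weeks of vildagliptin vs. glibenclamide treatment" and "Change in the central blood pressure from baseline to after 12 weeks of vildagliptin vs. glibenclamide treatment".

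Each outcome has its own pre-treatment value. Under Randomization and follow-up, before allocation, "50 individuals will be submitted to an evaluation of endothelial function using the Endo-PAT 2000 device and measurement of the arterial stiffness" by tonometry. Under Vascular tests: "Vascular tests will be performed in the subjects of both groups at the first visit and after 12 weeks of treatment". Table 2 schedules both measurements at Visit 1 and Visit 3.

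The Statistics section then names the methods. "Differences between the both groups at baseline will be evaluated by unpaired" *t* test or Mann–Whitney test. "The change from baseline to 12-weeks follow-up in the both groups will be evaluated using the paired" *t* test. A Pearson correlation relates HbA1c to RHI and AIx. The section names no model with a covariate and no test that compares the 12-week change between the arms.

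The sample size rests on "considering a 30 % change in the RHI between treatment groups as clinically relevant", an SD of 0.3, 80% power, a significance level of 0.05, 21 subjects in total and 20% dropout, ending at 25 per group. It gives no reference RHI and no correlation between baseline and week 12, and it does not say whether 0.3 is the SD of one RHI reading or of the change.

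**The concern.** A raw change score fixes the slope of the week-12 value on baseline at 1. If the true slope is below 1, as regression to the mean implies, the score over-corrects: the arm that happens to start with lower RHI appears to gain more. ANCOVA estimates the slope from the data and removes that component.

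The trial is small, about 25 × 0.8 = 20 completers per arm, so precision is scarce and visible chance imbalance in baseline RHI is plausible. The baseline significance test does not help, because its result does not enter the treatment estimate. The check of similarity between groups in the Statistics section governs only the Pearson correlation, and the variables it lists include neither baseline RHI nor baseline central pressure. The section gives no reason for leaving the baseline out of the comparison of change.

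**Working it through.** **1. The plan's own figure.** The stated requirement of 21 subjects in total does not reproduce from a two-sided two-sample t test with SD 0.3 and 80% power:
- An absolute difference of 0.30 needs 17 per arm (34 in total).
- A difference of 30% of 1.68, that is 0.504, needs 7 per arm (14 in total). The value 1.68 is the only RHI level in the document; it is a dysfunction cut-off, not a planning mean.
- The final 50 patients fit 21 *per group* (21 × 1.2 = 25.2). They do not fit 21 in total (21/0.8 = 26.25, so 27 in all).

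As a working assumption I therefore read 21 as per group and solve for the difference that gives 80% power (noncentral t): 0.266. This is back-calculated and is not stated in the protocol.

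**2. Variance.** Let σ be the single-reading SD, equal at both times, and n the number per arm.
- Change score: Var = (2/n) · 2σ²(1−rho)
- ANCOVA: Var = (2/n) · σ²(1−rho²)
- Ratio: (1−rho²) / [2(1−rho)] = (1+rho)/2, which is 0.65, 0.75, 0.85 and 0.95 at rho 0.3, 0.5, 0.7 and 0.9.

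**3. Power at 20 per arm, difference 0.266, two-sided 0.05** (38 degrees of freedom for the change score, 37 for ANCOVA). If 0.3 is the SD of change, the ANCOVA SD is 0.3·√((1+rho)/2). If 0.3 is a single-reading SD, the change SD is 0.3·√(2(1−rho)) and the ANCOVA SD is 0.3·√(1−rho²).

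| rho (assumed) | 0.3 = SD of change: change score → ANCOVA | 0.3 = single-reading SD: change score → ANCOVA |
|---|---|---|
| 0.3 | 78.0% → 92.3% (+14) | 63.6% → 81.6% (+18) |
| 0.5 | 78.0% → 88.3% (+10) | 78.0% → 88.3% (+10) |
| 0.7 | 78.0% → 84.1% (+6) | 94.1% → 96.9% (+3) |
| 0.9 | 78.0% → 79.9% (+2) | near 100% both (0) |

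**4. Other differences, with 0.3 as the SD of change.** At 0.30, power goes from 86.9% to 96.8%, 94.5% and 91.6% at rho 0.3, 0.5 and 0.7 (+10, +8, +5). At 0.504 it is 99.9% unadjusted, so the gain is about 0.

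**5. Precision at rho 0.5.** The 95% half-width is 2.024 × 0.300 × √(2/20) = 0.192 for the change score. For ANCOVA it is 2.026 × 0.260 × √(2/20) = 0.166.

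**6. Chance imbalance.** Given an observed baseline difference D, the change-score estimate is off by (1−rho)·D in the opposite direction. With a single-reading SD of 0.3 and 20 per arm, D has SD 0.3·√(2/20) = 0.095. At rho 0.5, a 1-SD imbalance shifts the estimate by 0.5 × 0.095 = 0.047, or 18% of 0.266.

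**7. Steps 2 and 6 describe one cost.** The variance difference in step 2 is (2/n)σ²(1−rho)², which is exactly (1−rho)² · Var(D). At rho 0.5 the change-score variance is 0.0090, the ANCOVA variance 0.00675 and the imbalance part 0.00225.

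**The case against.** - **The power loss is not a protocol figure.** A reader might conclude that the plan gives away about 10 points of power. The documents do not support that as an unconditional statement. It needs rho near 0.5, the per-group reading of 21, and the back-calculated 0.266. If 0.266 were 30% of a reference RHI, that reference would be about 0.89, well below the only RHI level in the document. With a difference near 0.5 the gain vanishes. This objection stands, and the size has to be given as a conditional range.
- **The change score is not biased.** A reader might infer that the analysis is invalid, or that imbalance is a second harm on top of the wider interval. Neither follows. Over randomisation the change score is unbiased and its type I error is held. Step 7 shows that the imbalance is already inside its interval.
- **The outcome definition is sound, and the unadjusted between-arm test is hypothetical.** A change-from-baseline outcome is compatible with ANCOVA: regressing the change or the week-12 value on treatment and baseline gives the same treatment estimate. The Statistics section names only a paired test for the change, so the power comparison is against the unpaired test that a reader would supply. Both remarks are right. The missing between-arm test is the larger gap, but filling it with an unpaired test of change would leave this point open.
- **A covariate could be left to the analysis plan.** This would answer silence. Here the section states which tests will be applied to the change, and all of them are unadjusted.
- **Central pressure has no planning values.** Correct. The power figures concern RHI only.

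**Conclusion.** The point holds as an efficiency improvement to a stated method, not as an error that invalidates the trial. For any rho below 1 with equal variances, ANCOVA on the baseline is more precise than raw change, and the variance ratio (1+rho)/2 needs no planning value except rho.

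The effect on power for RHI is conditional. Under the working assumptions it is roughly 3 to 18 points over rho 0.3 to 0.7 across both readings of the SD, at most about 2 at rho 0.9, and about 0 if the intended difference is near 0.5, where only the interval narrows. For central pressure the direction is the same under the same conditions, but no size can be given. The change is worth making because the baseline is already collected and scarce precision is forgone for no stated reason.

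**What to change.** In the Statistics section, state that the between-group comparison of each listed outcome is an ANCOVA (linear regression) of the week-12 value, or equivalently of the change, on treatment group and that outcome's own baseline: baseline RHI for RHI, baseline central pressure for central pressure. Report the adjusted mean difference with its 95% confidence interval. The paired tests can remain as within-arm description.

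The same sentence supplies the between-arm test that the section does not name. It needs no further patients, visits or measurements, and the SPSS software already named can fit the model. The statistical cost is one residual degree of freedom.

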## Statistical considerations

### Sample size and power calculations

The site http://www.lee.dante.br-pesquisa was used to estimate the sample size, considering a 30 % change in the RHI between treatment groups as clinically relevant. Assuming a standard deviation of 0.3 would require a total of 21 subjects to detect a 30 % change in the RHI with a power of 80 % at a significant level of 0.05. However, considering a potential 20 % of drop-out or lost to follow-up rate, a total of 50 patients (25 for each group) will be considered.

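### The sample-size paragraph contradicts itself: a total of 21 cannot become 50 through a 20% drop-out allowance, and 21 cannot be derived from the inputs given

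*Protocol article*

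**What the plan says.** All the figures stand in one short paragraph of the protocol article, under Sample size and power calculations.

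- Effect: "considering a 30 % change in the RHI between treatment groups as clinically relevant".
- SD and resulting number: "Assuming a standard deviation of 0.3 would require a total of 21 subjects to detect a" 30% change.
- Error rates: "with a power of 80 % at a significant level of 0.05". The Statistics section sets the sidedness: "For all analysis, a 2-sided *P* < 0.05 will be considered statistically significant".
- Loss: "considering a potential 20 % of drop-out or lost to follow-up rate".
- Final size: "a total of 50 patients (25 for each group) will be considered".

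The outcome that this size should serve is the 12-week change in RHI from baseline, vildagliptin versus glibenclamide (Outcomes and outcome adjudication). No mean RHI is given. The only RHI level in the article is a diagnostic cut-off, under Vascular tests: "Endothelial dysfunction will be defined as a RHI ≤ 1.68".

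**The concern.** Two things look wrong. First, adjacent sentences give a total of 21 and a total of 50, linked only by a 20% drop-out allowance that cannot bridge them. Second, the effect is a percentage while the SD is a bare 0.3. Without a mean RHI the effect has no size in RHI units, and without knowing which SD is meant the standardised effect is undefined.

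This paragraph is the article's only justification for the trial's size. If the trial finds no difference, readers will turn to it to learn which difference was ruled out with adequate power. As written, they cannot tell whether that was about 0.27, 0.30 or 0.50 RHI units.

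**Working it through.** **Inputs from the article.** Effect 30% of RHI; SD 0.3; power 80%; two-sided alpha 0.05; 1:1 allocation; loss 20%; 25 per group randomised.

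**Step 1: from 21 to 50.** The number to randomise is n/(1 − loss).

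| Reading of 21 | n/(1 − 0.20) | Shortcut n × 1.20 | Article |
|---|---|---|---|
| Total | 26.25, so 27 in total | 25.2 in total | 50 in total |
| Per group | 26.25, so 27 per group (54) | 25.2 per group | 25 per group (50) |

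As a total, 21 misses 50 by about half under either formula. As a per-group number, the shortcut gives 25.2, which matches 25 per group once rounded down. So 50 makes sense only if 21 is per group.

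**Step 2: completers on the per-group reading.** 25 × 0.80 = 20, one below 21. The difference that 21 per group detects with 80% power at SD 0.3 (two-sample t test) is 0.266 RHI units. With 20 per group, power for that same difference is 78.0%.

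**Step 3: can 21 be derived?** The per-group number is approximately n = 2(1.960 + 0.842)²(SD/delta)² = 15.70 (SD/delta)², checked here with the two-sample t test. The article does not give delta in RHI units, so each row is an assumption.

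| Assumed reading | delta | SD | n per group, t test (normal approx.) | Total, t test |
|---|---|---|---|---|
| 30% entered as 0.30 units | 0.30 | 0.30 | 16.7, so 17 (16) | 34 |
| 30% of 1.68, the cut-off used as an assumed mean | 0.504 | 0.30 | 6.7, so 7 (6) | 14 |

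Neither gives 21, as a total or per group. Other assumptions do come close. Suppose 0.3 is the SD of a single RHI measurement and the two measurements are uncorrelated. The SD of the change is then 0.3 × √2 = 0.42. With an assumed mean RHI of 1.7 to 1.8, the total is 19.4 to 21.7 by normal approximation, or 21.5 to 23.8 by t test. So 21 is not refuted; it just does not follow from what is stated.

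**Step 4: what 20 completers per group can detect** (two-sample t test, two-sided 0.05).

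| SD of the analysed variable | Difference detectable with 80% power | Power for 0.30 | Power for 0.504 |
|---|---|---|---|
| 0.3 (stated) | 0.27 | 87% | >99% |
| 0.4 (assumed) | 0.36 | 64% | 97% |
| 0.5 (assumed) | 0.45 | 46% | 87% |
| 0.6 (assumed) | 0.55 | 34% | 74% |

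Only the first row uses the article's SD. The others show why it matters which quantity 0.3 describes.

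**The case against.** The case on the other side has four parts.

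1. *A journal article condenses a fuller protocol, which may give the mean RHI and define the SD.* This is fair, and the missing mean alone would be a weak point. It does not excuse the clash between 21 and 50, which are both stated figures in the same paragraph.
2. *It is too strong to say that 21 is wrong.* This stands. With no mean and no definition of the SD, 21 can be neither confirmed nor refuted, and some assumed inputs reach it. Also, 1.68 is a cut-off taken from a study of healthy people, not an expected mean for these patients.
3. *The drop-out shortfall is trivial.* Largely true. It arises only if 21 is per group, and then it is one completer per group and about two percentage points of power. If 21 really is a total, 40 completers are nearly double the stated need.
4. *The low power figures rest on SDs that the article does not contain.* True. They illustrate sensitivity and are not estimates for this trial.

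A reader might also infer that the calculation was really run at 90% power, since delta = SD gives 21.01 per group at 90% by normal approximation. The article does not support this. It never states a delta of 0.30, the match holds only before rounding up, and the t test gives 22.0.

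**Conclusion.** The paragraph is wrong as written and should be corrected. A total of 21 with a 20% allowance gives 27, not 50; this needs no outside assumption. If 21 is per group, the only reading that explains 50, the allowance leaves 20 completers against 21 needed, and power is about 78% rather than 80%. The 21 itself is not derivable from the stated inputs.

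A reader might go further and infer that the trial is too small. The article does not show that. If the SD of the analysed change is 0.3, then 20 completers per group exceed both the 17 needed for 0.30 units and the 7 needed for 0.504. Power would fall below 80% for 0.30 units only if the relevant SD were appreciably larger than 0.3, and the article gives no figure for that. The fault lies in the stated justification, not in the number of patients.

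**What to change.** Keep 50 patients, 25 per group, and rewrite the paragraph:

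- State 21 as the per-group or total figure actually meant, and make the drop-out step agree with it.
- Keep the 30% effect, since it is the one called clinically relevant, but give it in RHI units together with the assumed mean RHI.
- Say whether 0.3 is the SD of RHI or of its 12-week change, and give its source.
- Say that the calculation is for the between-group comparison of change in RHI. The Statistics section names only a paired t test for change from baseline, so the wording of the two sections should be aligned.
- Restate the power at 20 completers per group. For reference, an SD of 0.3 for the analysed variable gives 80% power for 0.27 units.

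This costs wording only and adds no patients. The restated power may look less favourable if the SD of the change turns out to be larger than 0.3.
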